**Methods:**

This study is a multicentral randomized controlled trial. A total of 68 chronic persistent asthma patients will be randomly allocated into two groups: the Lung meridian group and the Heart meridian group. This trial will include a 2-week baseline period, a 4-week treatment period with 12 sessions’ acupuncture, and an 8-week follow-up period. The primary outcome is the Asthma Quality of Life Questionnaire (AQLQ). Secondary outcomes are the Asthma Control Test (ACT), Peak Expiratory Flow (PEF), and Forced Expiratory Volume in 1 s (FEV1). The AQLQ and ACT will be collected at baseline, week 4, week 8, and week 12 after randomization. PEF, FEV1, the Self-rating Anxiety Scale (SAS), and the Self-rating Depression Scale (SDS) will be assessed at baseline and week 4.

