Acupuncture, as a main complementary and alternative therapy, has traditionally been used to control asthma in China for thousands of years. Recently, accumulating evidence has supported the benefit of acupuncture for asthma [17, 18]. It is reported that acupuncture can significantly relieve the asthma-related symptoms, improve QoL, influence inflammatory cell counts [17], ameliorate of peak expiratory flow (PEF) variability [14], and increase the forced expiratory volume in 1 s (FEV1) [19]. However, most of these studies have focused on whether acupuncture is useful for asthma by comparing the efficacy differences between acupuncture and medication intervention [14, 18], or verum acupuncture and sham acupuncture [15, 17]. Few trials have involved the comparison of different acupuncture prescriptions to verify the efficacy differences between different acupuncture interventions.

According to the theory of traditional Chinese acupuncture, the Lung meridian connects with the lung directly, while the Heart meridian associates with the lung indirectly. Both the acupoints on Lung meridian and on the Heart meridian are commonly used for preventing and controlling asthma in clinical practice [20]. Hence, this multicenter randomized controlled trial focuses on the efficacy differences of the two acupoint prescriptions for treating asthma by evaluating the effectiveness of the acupoints on the Lung meridian compared to the acupoints on the Heart meridian, respectively, so as to provide high-quality evidence for a better acupuncture prescription selection and improve the curative effect.

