### Participants and recruitment strategy

Participants will be mainly recruited from inpatients and outpatients in the respiratory department of the First Affiliated Hospital of CDUTCM, the Fifth People’s Hospital of Chengdu and the First Affiliated Hospital of Anhui University of Traditional Chinese Medicine. The recruitment strategies also include delivering leaflets at outpatients, posting advertisements in communities, and distributing news on the website of the Chengdu University of TCM and our WeChat public account. All potential asthma patients diagnosed with the GINA criteria will take a physical examination, which includes an x-ray plate, lung function test, electrocardiograph, routine blood test, liver function test, kidney function test, blood immune test (IgE), and urine and feces routine tests. The respiratory physician will make the final diagnosis of potential patients.

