### Sample size

According to a previous study that investigates the therapeutic effect of acupuncture for asthma [23], the mean improvement of the AQLQ was − 2.75 ± 4.52 (mean ± SD) in the acupuncture group and 0.86 ± 4.95 in the control group. With a two-side significance level of α = 0.05 and power of 80%, 27 participants are required in each group. Allowing for a 20% dropout rate, 34 participants per treatment arm will be recruited, equaling 68 patients in total.

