### Data analysis

All data will be analyzed by an independent statistician using SAS 9.4 software (SAS Institute Inc., Cary, NC). All efficacy and safety analyses will be strictly conducted according to the intention-to-treat (ITT) principle. Multiple imputation will be used to deal with missing data. Continuous variables will be described with means and standard deviation (SD) or median, maximum, minimum, P25, and P75, as appropriate. And categorical variables will be described with percentage and frequencies.

The comparison between groups will be analyzed by the analysis of covariance (ANCOVA) if the change of outcomes from baseline to 4 weeks is normally distributed. The outcome variable will be the change of AQLQ from baseline to week 4, and covariates will be age, gender, duration of disease, and the expectation of acupuncture in the ANCOVA analysis. The non-parametric ANCOVA will be conducted if the change is not normally distributed. The comparisons between time points within groups will be analyzed using the paired sample *t* test or Wilcoxon rank-sum test, as appropriate. Separate ANCOVA analyses will be performed for each secondary outcome, the AQLQ and ACT at week 8 and week 12 follow-up. Categorical variables will be analyzed using the chi-squared test or Fisher’s exact test, as appropriate.

The center effects will be included in the analysis model. A subgroup analysis between inpatient and outpatient participants in each group will be performed exploratively. Statistical results will be presented as point estimates of effect sizes accompanied by confidence intervals.

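### The exploratory subgroup analysis, read literally, compares inpatients with outpatients inside each arm, so it does not estimate whether the Lung-versus-Heart difference varies by setting

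*Protocol article*

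**What the plan says.** The only statement on subgroups is in the protocol article, Data analysis: "A subgroup analysis between inpatient and outpatient participants in each group will be performed exploratively".

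Three other places fix its meaning:

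- The abstract (Methods) says patients are "randomly allocated into two groups: the Lung meridian group and the Heart meridian group". Study design and Acupuncture interventions use the word group in the same way. Within Data analysis itself, comparisons between groups are Lung versus Heart, and comparisons within groups are made inside one arm.
- The Background gives the aim as "evaluating the effectiveness of the acupoints on the Lung meridian compared to the acupoints on the Heart meridian".
- For the ANCOVA, "covariates will be age, gender, duration of disease, and the expectation of acupuncture in the ANCOVA analysis", and "The center effects will be included in the analysis model". Neither setting nor an arm-by-setting term is named anywhere.

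On where the two settings come from, Participants and recruitment strategy says "Participants will be mainly recruited from inpatients and outpatients in the respiratory department". The expected split is not given.

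**The concern.** Setting is not randomised. Inpatients and outpatients may change by different amounts over four weeks whichever points are needled. An inpatient-minus-outpatient difference inside one arm therefore contains the prognostic effect of setting, and one arm's data cannot separate that from a difference in treatment effect.

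The trial is meant to guide the choice between two prescriptions. The subgroup question that serves this aim is whether the Lung-minus-Heart difference is the same in inpatients and outpatients. The stated contrast does not estimate that. What is at stake is interpretation: a setting difference that stands out in one arm and not in the other could be taken to mean that one prescription suits one kind of patient, when prognosis and small numbers would be enough to produce it.

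**Working it through.** **Inputs from the protocol article (Sample size).** Mean changes −2.75 (SD 4.52) and 0.86 (SD 4.95); two-sided α 0.05; power 80%; 27 per arm; 34 per arm after 20% dropout; 68 in total.

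**Assumptions, not in the documents.** The inpatient share, equal in both arms: 4 to 17 of 34 for the disagreement rates, 10% to 50% for the power figures. The setting difference in change: 0, 0.5 or 0.8 SD, the same in both arms. Outcomes are normal with a common SD, there is no covariate adjustment, and all 34 per arm are analysed unless stated.

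**1. The plan's own figure.** The difference is 2.75 + 0.86 = 3.61. The pooled SD is √((4.52² + 4.95²)/2) = 4.74. Then n = 2 × (4.74 × (1.96 + 0.8416)/3.61)² = 27.06 per arm, which rounds up to 28 against the stated 27. Power at 27 is 79.9% (normal) or 78.4% (noncentral t). 27/0.8 = 33.75, so 34 per arm and 68 in total. The stated size is reproduced to within one patient per arm. No figure is given for the subgroup analysis.

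**2. The two contrasts.** Write the mean change as L or H (arm) with subscript in or out (setting).

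- As written: L_in − L_out, and separately H_in − H_out. Each has SE = SD × √(1/n_in + 1/n_out).
- Effect modification: (L_in − H_in) − (L_out − H_out), with SE = SD × √(2/n_in + 2/n_out).

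If setting shifts both arms by the same amount, each within-arm contrast equals that shift and the interaction is zero. The second line is the difference of the two contrasts in the first, but the plan does not say that this difference will be taken.

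**3. How often two within-arm tests would disagree with no effect modification.** The arms contain different patients, so the two tests are independent. With the same numbers in each arm they have equal power p, and exactly one is significant with probability 2p(1 − p), which cannot exceed 50%. Here p comes from the noncentral t with 32 df and noncentrality δ/√(1/n_in + 1/n_out), with δ in SD units.

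| Inpatients : outpatients per arm | δ = 0 | δ = 0.5 | δ = 0.8 |
|---|---|---|---|
| 4 : 30 | 9.5% | 25.4% | 42.6% |
| 11 : 23 | 9.5% | 38.7% | 49.2% |
| 17 : 17 | 9.5% | 41.4% | 47.2% |

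For 11 : 23 at 0.5 SD, p = 0.263 and 2 × 0.263 × 0.737 = 0.387. At 0.8 SD, p = 0.562 and 2 × 0.562 × 0.438 = 0.492.

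**4. Check on the planning scale.** In 40,000 simulated trials with 17 inpatients and 17 outpatients per arm, SD 4.74, a setting difference of 3.61 in both arms and no interaction, exactly one within-arm test was significant in 49%, at least one in 82%, and the interaction test in 5.1%.

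**5. Precision of the replacement.** With SD 4.74, the power shown is for an interaction of 3.61 (normal approximation):

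| Inpatient share | SE of interaction, 34 per arm | Power, 34 per arm | Power, 27 per arm |
|---|---|---|---|
| 50% | 2.30 | 35% | 29% |
| 30% | 2.51 | 30% | 25% |
| 20% | 2.87 | 24% | 20% |
| 10% | 3.83 | 16% | 13% |

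The SE of the overall between-arm difference at 34 per arm is 4.74 × √(2/34) = 1.15, so the interaction is at best estimated with twice that error.

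**The case against.** **The wording may just be loose.** The sentence could be meant as the planned Lung-versus-Heart analysis broken down by setting, which would fit the aim. That reading is possible and cannot be excluded, but the text does not say it. It names inpatients and outpatients as the two sides of the comparison and places them inside each group. If the looser reading was intended, the rewording is a clarification and costs nothing.

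**No misreading is planned.** A reader might infer that the investigators will test each arm, compare the two p-values and claim that one prescription works better in one setting. The documents do not support this. They name no test for this analysis, do not call it a test of effect modification, and promise estimates with confidence intervals. The disagreement rates above are therefore conditional: they show what would happen if the two results were compared by significance. Two within-arm estimates with intervals would also let a reader form the unadjusted interaction.

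**A prognostic description is legitimate.** Describing who improves on a given prescription is not wrong in itself. That stands, but it does not tell a clinician which prescription to choose in which setting.

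**It is exploratory, and details may sit elsewhere.** The label limits the weight of the result; it does not change what the contrast estimates. The point concerns a contrast that the article states, not one that it leaves out.

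**The interaction will be imprecise.** This is correct, and it limits what the fix can deliver.

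**Conclusion.** The point holds as a minor finding. Taken literally, the stated subgroup contrast is prognostic and does not address whether the Lung-versus-Heart difference varies by setting. Nothing else in the article corrects it.

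The size rests on an assumed inpatient share and assumed setting differences, because the article gives neither. Over the ranges shown, comparing the arms by significance would give a false contrast between them in roughly a quarter to a half of trials once the settings differ by 0.5 to 0.8 SD. The interaction test keeps its 5% error rate. Dropout would change these figures, since they use all 34 per arm.

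It would be too strong to say that this undermines the trial's main result. The primary ANCOVA, the sample size and the stated decisions do not depend on this analysis.

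**What to change.** Replace the subgroup sentence in Data analysis with:

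*The Lung-minus-Heart difference in AQLQ change to week 4 will be estimated with 95% CI within inpatients and within outpatients from the primary ANCOVA plus setting and an arm-by-setting term; the interaction estimate and CI will be reported as exploratory, and inpatient-versus-outpatient differences within arms will not be interpreted as differences in treatment effect.*

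This costs one sentence and uses the same data and the same 68 patients. The drawback is the low precision shown above, so the interaction should be reported as an estimate with its interval and not used as a basis for choosing a prescription by setting.

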### Patient safety

Participants with fainting, infection, or other severe adverse events should be discontinued from treatment and processed immediately. Any adverse events will be recorded by patients, acupuncturists, and outcome assessors. Acupuncture related adverse events include bleeding, dizziness, pain, infection, and so on. Besides, any other severe events also will be recorded in the CRFs in detail and be monitored by the Ethics Committees.

### Quality control

The trial protocol is reviewed and revised by the experts in acupuncture, methodology, pneumology, and statistics. The related staff will be trained using a prespecified standard operating procedure. The compliance of patients will be improved through health education and timely follow-up. The outcomes will also be evaluated by outcome assessors if the participants discontinue acupuncture or deviate from protocol.

## Discussion

This is the first RCT focused on the efficacy differences of the acupoints on the Lung meridian compared to the acupoints on the Heart meridian for treating chronic persistent asthma. The results will provide evidence for acupuncture prescription selection and the clinical efficacy improvement. The results of this trial will also be used to determine whether or not a full definitive trial will go ahead, which will further confirm the theory of Meridian-viscera Association.

The theory of Meridian-viscera Association emphasizes the diagnostic and therapeutic values based on the mutual relation in physiology and pathology between meridians and viscera. That is, visceral physiological functions and pathological changes will manifest in the corresponding meridians or the acupoints [34], and the visceral disorders can be treated with the involved meridian and acupoints [35]. The lung is close to the heart anatomically, so the two viscera have close association physio-pathologically. Based on the theory of Meridian-viscera Association and clinical practice, the Lung meridian and the Heart meridian are the commonly used meridians for pulmonary disorders including asthma [17, 18]. Hence, this study will select Taiyuan (LU9), Lieque (LU7), and Chize (LU5) on the Lung meridian and Shenmen (HT7), Yinxi (HT6), and Shaohai (HT3) on the Heart meridian for the following reasons: (1) these acupoints have been proved to be effective in improving QoL and relieving symptoms of asthma patients [18, 23], (2) all of these acupoints are specific acupoints on the two meridians, and (3) the selected acupoints are on the medial side of the upper arm and at the same nerve segment based on the modern anatomy so as to minimized the bias of comparison.

The efficacy evaluation will be performed from the following three aspects: the quality of life, symptoms, and emotion of asthma patients. Asthma affects patients’ daily life seriously [4]; the improvement of QoL is essential for asthma patients, especially chronic persistent asthma patients. So the AQLQ will be assessed as the primary outcome, which is a reliable, valid, discriminating, and responsive measurement and is more sensitive than the 36-Item Short Form Survey (SF-36) questionnaire in detecting differences in asthma severity [36]. At the same time, the ACT, PEF, and FEV1, as secondary outcomes, will be evaluated before and after treatment in this trial. Patients with poor-controlled or uncontrolled asthma have more serious symptoms and worse lung function [37]. Hence, ACT will be performed to identify patients with poorly controlled asthma [26, 27], and PEF and FEV1 will be used to assess the severity of lung function in asthma patients [29, 30]. Moreover, anxiety and depression are emotional common disorders accompanied by adult asthma [38, 39]. So the SAS [31] and SDS [32] are used to assess the emotion of asthma patients.

### Trial status

This trial is registered on the Chinese Clinical Trial Registry (http://www.chictr.org.cn) on 7 November 2019 (Registered number: ChiCTR1900027284, the protocol version number: V2.0). The patient recruitment of this trial has not been started and will begin on November 25, 2019, and will be completed on October 31, 2021.

## Data Availability

The data and materials during the current study are available from the corresponding author on reasonable request.

## Abbreviations

ACT: Asthma Control Test
ANCOVA: The analysis of covariance
AQLQ: Asthma Quality of Life Questionnaire
CDUTCM: Chengdu University of Traditional Chinese Medicine
CONSORT: The Consolidated Standards of Reporting Trials
CRFs: Case Report Forms
FEV1: Forced Expiratory Volume in 1 s
FVC: Forced Vital Capacity
GINA: Global Initiative for Asthma
ITT: Intention-to-treat analysis
PEF: Peak Expiratory Flow
QoL: Quality of Life
RCT: Randomized Controlled Trial
SAS: Self-rating Anxiety Scale
SD: Standard Deviation
SDS: Self-rating Depression Scale
SF-36: 36-Item Short Form Survey
SPIRIT: Standard Protocol Items Recommendations for Intervention Trials
STRICTA: Standards for Reporting Interventions in Clinical Trial of Acupuncture
TCM: Traditional Chinese Medicine
